#### Secondary Outcome Measures

The primary outcome will help us to meet secondary objective A. Based on the results for usability, we will establish what types of exercise are usable for each fall-risk group to determine the best intervention modalities for different fall-risk groups in future interventions.

The secondary outcome measures for secondary objective B are the health care team’s perception of the difficulty of carrying out the intervention and the time spent by the health care team on the physical activity intervention. A 5-point scale of perceived difficulty will be assessed after each session, including “very easy,” “easy,” “feasible,” “difficult,” and “impossible.” A scale will also be assessed after each session to quantify the time spent with the patient (ie, the time to complete the physical activity monitoring form, verify the time spent out of bed, and have the patient perform the balance and transfer exercises), including “0 to 2 minutes,” “3 to 5 minutes,” “6 to 10 minutes,” “11 to 20 minutes,” and “>20 minutes.” These scales have not been scientifically validated.

The intervention will be considered feasible if the health care team consider a majority of sessions to have had a difficulty between “very easy” and “feasible” and if a majority of sessions were shorter than 10 minutes.

The secondary outcome measures for secondary objective C are the percentage of patients who completed the FTSS test before and after the intervention and the time in seconds (measured before and after the intervention) the patients needed to complete the FTSS test. We will consider the intervention beneficial for patients’ lower-limb strength in two cases: if the patients can complete the FTSS test more often after the intervention than before, and if those who complete the FTSS test can do so more quickly after the intervention than before.

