#### Secondary Objectives

There are 3 secondary study objectives. Secondary objective A will be to determine the difficulty level of the physical exercises in each fall risk group and analyze the usability of the intervention in each group to determine the best intervention modality for each group. Secondary objective B will be to determine the health care team’s perception of the difficulty of carrying out the intervention and analyze their perceptions with 2 scales. Secondary objective C will be to examine the effects of this physical activity intervention on the patients’ lower-limb strength, comparing their ability and time to perform the Five Times Sit to Stand (FTSS) test before (measured during a clinical assessment) and after the intervention (on the last day of hospitalization or the 20th day of hospitalization, if the patient is still hospitalized).

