### Monitoring of the Implementation of the Physical Activity Program

Nurses are in charge of keeping a physical activity monitoring form up to date, which is also digitized in the computerized patient medical file and added to the case report form. This form includes the following information: date of daily physical activity session; level of completion for each type of exercise; reasons why the daily objectives were not reached during the session; perceived feasibility of the daily session by the caregiver; time spent by the caregiver conducting the daily session; and occupational category of the caregiver who supervised the daily session, including nursing assistant, nurse, physiotherapist, occupational therapist, paramedical student, and second-cycle (equivalent to a master’s degree in medical sciences) medical student.

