### Outcomes

#### Primary Outcome Measure

The primary outcome measure is the number of participants in each fall risk group who complete 75% or more of the physical activity program for each type of exercise during hospitalization. For each type of exercise, success is quantified daily as follows: for exercise 1, the participant was able to stay out of bed for at least 3 hours; for exercise 2, the participant stood in static balance for at least 2 minutes in front of the chair, holding the back of the chair; and for exercise 3, the participant switched from sitting on a chair to standing at least 5 times. The percentage represents the ratio between the number of days when the patient successfully completes a type of exercise and the total number of days of hospitalization. For each fall risk group and each type of exercise, the intervention will be defined as usable if at least 80% of the participants complete at least 75% of the exercise. These thresholds have not been scientifically validated.

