#### Descriptive Analyses

A diagram will be used to summarize the progress of the study as patients are added and to monitor the protocol. All the clinical characteristics of the participants (such as age, sex, and weight) and the results of the investigations carried out will be described. A table will be used to summarize the level of completion of the physical activity intervention for each fall risk group and each type of exercise. This will help us to determine which type of exercise is most usable for each fall risk group (secondary objective A). A contingency table will be used to report, for each fall risk group, the perceived difficulty of the daily sessions by the health care team and the time spent on carrying them out. A contingency table will also be used to report, for each fall risk group, the number of FTSS tests completed by the patients at the beginning of the intervention, the sixth day of the intervention, and at the end of the intervention.

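### Secondary objective A is meant to measure exercise difficulty, but its only assigned measure is completion, which does not separate inability from non-delivery; the reasons already recorded would help (minor)

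*Protocol article*

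**What the plan says.** - **Objective.** The Secondary Objectives section states: "Secondary objective A will be to determine the difficulty level of the physical exercises in each fall risk group". The same sentence goes on to usability and the choice of modality for each group. The Discussion restates objective A as how exercise difficulty varies with fall risk level.
- **Measure.** Secondary Outcome Measures says "The primary outcome will help us to meet secondary objective A", and then "Based on the results for usability, we will establish what types of exercise are usable for each fall-risk group". Descriptive Analyses ties objective A to one table, completion by risk group and type of exercise.
- **Construction of the measure.** Primary Outcome Measure defines the percentage as "the ratio between the number of days when the patient successfully completes a type of exercise and the total number of days of hospitalization". The decision rule is that "the intervention will be defined as usable if at least 80% of the participants complete at least 75% of the exercise".
- **Data collected.** The daily monitoring form records "level of completion for each type of exercise; reasons why the daily objectives were not reached during the session".
- **The one difficulty rating.** The 5-point scale in Secondary Outcome Measures is rated by the health care team once per session, for all exercises together, and belongs to objective B.

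**The concern.** Difficulty and completion are different quantities. An exercise may go uncompleted because the patient cannot do it, because the patient declines, or because the ward did not run it that day. The completion ratio gives all three the same weight. If it is read as difficulty, an exercise that patients could do but were not always offered looks harder than it is.

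The stake is how the result is interpreted. Secondary Outcome Measures says the findings will guide the choice of modalities for each risk group in future interventions, and the end of the Discussion foresees a larger study. The Results section already words its first impression in terms of what each group was able to complete, which is the step from completion to ability that the ratio alone cannot support.

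**Working it through.** The plan states no figure on this point, so there is nothing to reproduce. The check has two parts.

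**1. Does any planned measure separate inability from non-delivery?**

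- The primary ratio does not. Its denominator is all hospitalization days, so every day without success counts against the exercise, whatever the cause.
- The completion table in Descriptive Analyses shows more than the 75%/80% verdict, but it is still completion.
- The staff difficulty scale is given per session, so it cannot rank three exercises.
- The recorded reasons could separate the causes, but neither the outcome sections nor the Statistical Methods section uses them.

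**2. How much could non-delivery matter?** (illustration only)

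Input from the document: the 75% and 80% thresholds. Assumed, because the document does not give them: daily ability *a*, the share *m* of days lost for non-patient reasons, and length of stay *D*.

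*Expected completion* = a × (1 − m). It falls below 75% when m > 1 − 0.75/a.

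- a = 1.00: m > 1 − 0.75 = 25%.
- a = 0.90: 0.75/0.90 = 0.833, so m > 16.7%.

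*Share of fully able patients reaching 75%*, treating days as independent: P(X ≥ r), with X ~ Binomial(D, 1 − m) and r = 0.75 × D rounded up.

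| Stay (days) | r | m = 10% | m = 15% | m = 20% | m = 25% |
|---|---|---|---|---|---|
| 7 | 6 | 85.0% | 71.7% | 57.7% | 44.5% |
| 10 | 8 | 93.0% | 82.0% | 67.8% | 52.6% |
| 14 | 11 | 95.6% | 85.3% | 69.8% | 52.1% |
| 20 | 15 | 98.9% | 93.3% | 80.4% | 61.7% |

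True difficulty is nil in every cell. At 10% lost days all four stays remain above the 80% line. On this grid the line is first crossed at 15% for a 7-day stay, at 20% for 10- and 14-day stays, and at 25% for a 20-day stay.

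*Effect of removing undelivered days*, for a 10-day stay and 90% daily ability. The number of delivered days K is Binomial(10, 1 − m). Given K, successes are Binomial(K, 0.90), and 75% of K days is required.

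| m | All days in the denominator | Undelivered days removed |
|---|---|---|
| 0% | 93.0% | 93.0% |
| 10% | 70.8% | 93.8% |
| 20% | 43.8% | 92.4% |

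The first column moves with delivery although ability is fixed. The second stays close to what ability alone gives; its small movements come from rounding the 75% requirement to whole days.

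**The case against.** The strongest reply is that objective A is in practice a usability objective. The second half of its sentence, Secondary Outcome Measures and Descriptive Analyses all speak of usability, and the introduction names staff availability as part of what makes an intervention workable. Counting undelivered days is then reasonable. This stands for the primary rule, which should not change. It does not cover the word difficulty, which the Secondary Objectives section and the Discussion both use.

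The article also says the primary outcome will help meet the objective, not that it suffices, and a fuller document might tabulate the reasons. That softens the point. It does not remove it, because the article itself names the measure and table for objective A, and neither isolates difficulty.

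Three stronger readings are tempting, but the document does not support them:

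- **Missed sessions fall mainly on exercises 2 and 3, because exercise 1 needs no supervision.** The Abstract and the Intervention section put all three exercises under staff supervision, and checking time out of bed is counted in caregiver time. Uneven loss is possible but not shown.
- **Exercises will be labelled too difficult and dropped.** No section says so. The stated use is to choose modalities for future interventions.
- **The calculations show that a verdict in this trial is wrong.** They rest on assumed loss rates, stays and abilities. The document neither lists the categories of reasons nor gives their frequency.

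A practical objection also stands: reasons are recorded for a session, so a day with no session or no form may have none.

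**Conclusion.** The point holds as a mismatch between an objective and its measure. Objective A asks about difficulty, and the only assigned measure mixes inability with refusal and non-delivery. Data that could largely separate them are already collected but have no stated use. The usability rule is not affected.

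The size in this trial is unknown. If few days were lost for non-patient reasons, the completion table will approximate ability reasonably well. At loss rates of roughly 15% to 25%, depending on stay, an exercise with no difficulty at all could miss the 80% line. Those rates assume independent days, fully able patients and fixed stays, so they show sensitivity and are not an estimate. The recorded reasons would show how much loss there was, as far as they are complete. Minor, and cheap to improve.

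**What to change.** Keep the primary rule unchanged. For objective A:

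1. Add to the completion table, per exercise and risk group, the non-completed patient-days by recorded reason: patient unable (including pain or fatigue); refused; not delivered or organisational; no reason or no form recorded.
2. Fix the coding before analysis. The article says recruitment is closed and results are not yet analyzed, so this is still possible.
3. Base statements about difficulty on the patient-unable days, and show refusals separately, since refusing is not plainly difficulty.
4. Report completion with and without the days not delivered.

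If this is not done, describe objective A as usability only and drop the claim to difficulty.

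The cost is coding work and a larger table. If reasons were recorded per session rather than per exercise, which should be checked, a coding rule is needed for days when some exercises were completed and others were not. Days without a session may have no reason and must be shown as such, not reassigned. No clustered model is required for this descriptive objective.

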## Methods

### Design

This is an open-label, unicenter, nonrandomized, usability prospective clinical trial. There is no comparator group (ie, no control group). Figure 1 illustrates the trial design and Table 1 summarizes the timing of the trial. The intervention tested in this study is a physical activity intervention based on the physical acts of daily life that focuses on strengthening the lower-limb muscles and improving postural balance. It consists of 3 types of physical exercise that can be adapted to the fall risk level. It is offered to 3 categories of hospitalized patients, classified according to their risk of falling: low, moderate, and high. It is carried out from the second day of hospitalization after an assessment of the patient’s risk of falling until the last day of hospitalization or the 20th day of hospitalization if the patient is still hospitalized. In summary, this study consists of an inclusion visit, a physical activity program performed daily until the 20th day of hospitalization, and an end-of-study visit.

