### Intervention

This intervention follows the main principles of the latest French National Authority for Health (HAS) recommendations on the prevention of falls in older people [11]. Each fall risk group of participants will receive a physical activity intervention, carried out once a day, consisting of 3 types of exercise. In exercise 1, the participant must stay out of bed for at least 3 hours. This length of time prevents acute postural disorders that increase the risk of falling; these can occur when older patients are bedridden for too long. In exercise 2, the participant stands in static equilibrium for 2 minutes in front of a chair, holding the back of the chair. Depending on the participant’s abilities, the exercise is done standing on one or both feet. Exercise 3 requires the participant to switch from sitting on a chair to standing 5 times (this is similar to the FTSS test but is not timed). Depending on the patient’s abilities, the exercise is done with or without physical assistance.

This daily intervention is carried out starting on the day after informed consent is obtained from patients fulfilling the selection criteria. It is carried out under the supervision and monitoring of the health care team, specifically nurses and nursing assistants.

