#### Clinical Assessments

Clinical assessments are performed at inclusion and during follow up (Table 1). Except for the FTSS test, which is applied during follow up and at the end of the study, all clinical assessments are carried out as part of usual care. Clinical data are collected from the computerized patient medical file or directly from the participant if the data have not yet been added to the file.

The clinical assessment at inclusion will include the reason for hospitalization (including organ failure, musculoskeletal disorders or falls, neuropsychiatric disorders, medicosocial problems, or other causes); age and gender; anthropometric data (ie, weight and height); body mass index (kg/m^2^); and the Mini-Mental State Examination (MMSE) [15] score. The MMSE is used to assess cognitive function. It consists of 30 questions in 5 sections (orientation, memory and recall, attention, calculation, and language), with a final score graded out of 30 points. In the absence of memory complaint, (self-reported or non–self-reported), a final score between 27 and 30 indicates the probable absence of a cognitive disorder.

Clinical assessments at inclusion and during follow up will include the use of psychotropic drugs (eg, antidepressants, benzodiazepines, hypnotics, and neuroleptics); the number of different therapeutic classes of drugs taken; the FTSS test; and the patient’s overall pain, assessed using a verbal 6-point scale: “no pain,” “low pain,” “moderate pain,” “high pain,” “extreme pain,” and “not assessable.” The pain assessment is used to verify changes in pain level during hospitalization. The FTSS test measures a patient’s physical transfer ability. The test is to stand up from a chair 5 times as quickly as possible without pushing off. Performance is measured in seconds, from the initial seated position to the final seated position after having completed standing up 5 times. A time longer than 15 seconds is abnormal and is associated with physical and cognitive impairment [16].

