
Our study presents several limitations that have already been identified. First, it was not possible to quantify the type of activities carried out during exercise 1. Managing the specific activities in this exercise would have taken too much time for the caregivers. Second, the modality of the other two exercises was not well detailed. Because of the diversity of the patients, it was necessary to let the caregivers adapt the exercises. This caused us to lose several interesting types of data (eg, the number of trials needed to reach 2 minutes or the number of times an exercise was performed on one or both feet). Third, we did not use validated scales to evaluate the perceived feasibility from the point of view of the health care team. Nevertheless, we consider that the scales we used were informative. Finally, we used only the FTSS test to assess lower-limb strength. It would have been more interesting to use the Short Physical Performance Battery [22], which includes the FTSS test.

If we verify our hypotheses on usability and if we observe a beneficial effect for the patients, we will plan a larger-scale experiment in which we will investigate the effects of this type of intervention during and after hospitalization on the risk of falling, level of frailty, level of autonomy, length of stay in the geriatric acute-care unit, recurrence of falls, and rehospitalization. Such a study would allow us to better define the frequency, intensity, time, and type of exercise for patients with different fall risk levels.

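### The FTSS rule labels the programme beneficial from before/after change alone; with no comparator that change cannot be attributed to the programme, and the direction of the bias is unknown

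*Protocol article*

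**What the plan says.** All references are to the protocol article.

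- **Design:** "There is no comparator group (ie, no control group".
- **Secondary Objectives:** objective C is worded causally. It "will be to examine the effects of this physical activity intervention" on lower-limb strength, comparing the FTSS before and after.
- **Secondary Outcome Measures, first condition:** the programme will be judged beneficial for "lower-limb strength in two cases: if the patients can complete the FTSS test more often after the intervention than before".
- **Secondary Outcome Measures, second condition:** this one concerns speed and is joined to the first by *and*. It is met "if those who complete the FTSS test can do so more quickly after the intervention than before". No margin, test or confidence bound is attached to either condition.
- **Table 1:** the FTSS is done at enrolment, on day 6 of follow-up, and at study end (discharge or day 20).
- **Intervention:** exercise 3 is five sit-to-stands once a day; "this is similar to the FTSS test but is not timed". Depending on ability, "the exercise is done with or without physical assistance".
- **Clinical Assessments:** the test itself is stricter. "The test is to stand up from a chair 5 times as quickly as possible without pushing off".
- **Introduction, Context:** older inpatients are said to lose everyday abilities quickly, including rising from a low position.
- **Statistical Methods, General:** an overall two-sided .05 level and a confidence interval around means, neither linked to the benefit rule.
- **Discussion, final paragraph:** if usability is confirmed and "if we observe a beneficial effect for the patients, we will plan a larger-scale experiment".

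**The concern.** The rule turns a before/after difference into a statement about what the programme did. Between the two measurements an acute-care inpatient is treated for the admitting illness, may recover from it, may lose function through the hospital stay, takes part in the programme, and repeats both a similar movement and the test. The difference is the sum of all of these.

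No planned analysis separates them. The comparison between fall risk groups sets groups against each other, and every group receives the programme. The adjusted effect of physical activity mentioned under Primary Objective Analysis has no unexposed patients to be estimated from. The limitations listed in the Discussion do not mention the missing control.

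At stake is a published conclusion that the exercises improve lower-limb strength, and its use as one of the conditions for a larger study. The wording also leaves the rule itself open: two cases, joined by *and*, may mean that either condition suffices or that both must hold.

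**Working it through.** **The plan's own figures.** None is given for the FTSS: no expected completion rate, change, SD or power. The only design figure, 3 × 110 = 330, is described as empirical and does not bear on this rule. The probabilities below therefore rest on assumed inputs and are illustrations.

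**Inputs**
- From Results: group sizes 75, 105 and 85; pooled 75 + 105 + 85 = 265.
- Assumed: baseline completion p = 30% or 60%; SD of paired time change 6 s; proportions g and l of all patients in the group who gain or lose the ability to complete the test; mean gain in speed d (seconds); time changes drawn independently of gains and losses in ability.

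**Formulas**
- Condition 1 (more completers after than before): the number of patients who change status is Binomial(n, g + l), and the condition is met when gains exceed losses. If g = l, its probability is (1 − P(tie))/2.
- Condition 2 (completers quicker on average, paired): Φ(d / (6/√m)), with m ≈ n(p − l) patients completing both tests.
- With c1 and c2 the two probabilities: either = 1 − (1 − c1)(1 − c2); both = c1 × c2.

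**No true change (g = l = 5%, d = 0)**
- n = 75: P(tie) = 0.148, so c1 = (1 − 0.148)/2 = 0.426; c2 = 0.500.
- Either = 1 − 0.574 × 0.500 = 0.713; both = 0.213.

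**Modest recovery or practice, no programme effect (g = 10%, l = 5%, d = 1 s)**
- n = 75, p = 30%: c1 = 0.838; m = 75 × 0.25 = 18.75; c2 = Φ(1/1.386) = 0.765. Either = 1 − 0.162 × 0.235 = 0.962; both = 0.641.
- n = 105, p = 60%: c1 = 0.888; m = 105 × 0.55 = 57.75; c2 = Φ(1/0.790) = 0.897. Either = 0.989; both = 0.797.

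A simulation of 20,000 trials per setting agrees to within about one percentage point and gives these ranges over the three group sizes and both baseline rates:

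| Scenario | At least one condition | Both conditions |
|---|---|---|
| No true change, per group | 71-72% | 21-23% |
| Modest recovery, no programme effect, per group | 96-99% | 63-80% |
| Modest recovery, no programme effect, pooled n = 265 | over 99% | 89-96% |

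**With a two-sided .05 test added to each condition.** Under no change, at least one condition is met in the favourable direction about 5% of the time. Under modest recovery, pooled, it is still met 68-79% of the time; under stronger recovery (g = 15%, l = 5%, d = 2 s), pooled, 99% or more. The test removes chance verdicts and leaves attribution untouched.

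**The opposite case.** Mirror the modest scenario: g = 5%, l = 10%, completers 1 s slower. Suppose patients would have declined further without the programme, so that it works.
- n = 75, p = 30%: c1 = 0.098; m = 75 × 0.20 = 15; c2 = Φ(−1/1.549) = 0.259. Either = 1 − 0.902 × 0.741 = 0.332; both = 0.025.
- n = 105, p = 60%: c1 = 0.070; m = 105 × 0.50 = 52.5; c2 = Φ(−1/0.828) = 0.114. Either = 1 − 0.930 × 0.886 = 0.176; both = 0.008.

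A programme that reduces decline would usually fail the rule. Pass or fail follows the net course of the patients, whatever the programme contributed.

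**The case against.** The strongest reply has four parts.

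1. **The objective is secondary and exploratory.** The Discussion speaks of potential benefits, and the benefit condition is added to usability, so it makes the step to a larger study harder, not easier. That study would itself investigate effects. This stands and limits the weight of the point. It does not make the stated verdict supportable.
2. **The general section sets a .05 level and plans intervals.** A reader might infer that any numerical improvement will count. The text does not establish this: the rule is silent, and its link to a test may lie in a fuller document. The attribution problem remains under either reading.
3. **The bias need not be upward.** A reader might assume that recovery and regression to the mean inevitably flatter the programme. The documents do not support this. The Introduction describes functional loss in hospital, and eligibility does not select on FTSS performance, so regression to the mean has no stated basis. Recovery itself is an inference from the acute-care setting. Nor is passing the rule near-certain: both conditions are met in only 63-80% of cases per group under modest recovery.
4. **Exercise 3 is not the test.** A reader might say that patients rehearse the FTSS every day. The exercise is untimed and may be assisted, whereas the test is timed and done without pushing off. Improvement through repeated sit-to-stands is also partly the intended effect. What stands is familiarity with a similar movement and with a test given up to three times.

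**Conclusion.** The point holds as one of attribution. The plan states a benefit verdict that rests only on before/after change in a trial without a comparator, and it carries that verdict into the decision on a larger study. The verdict can be wrong in both directions.

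That the design cannot attribute the change follows from the text alone and needs no assumption. The probabilities do rest on assumptions: baseline completion, SD of change, the amount of recovery, and independence of the two conditions. They show scale and do not predict the result. The ambiguity between one condition and both matters in its own right: under no change it moves the chance of a favourable verdict from about 21-23% to about 71-72% per group.

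The primary usability verdict and the staff feasibility outcomes are not affected. This should be corrected before the results are reported, but it does not threaten the trial's main conclusion.

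**What to change.** Recruitment is closed, so a concurrent control cannot be added. The article says the results had not been analysed, so the wording can still change.

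1. **Secondary Outcome Measures:** replace the benefit rule with a description of within-patient change in FTSS ability and in FTSS time, paired and with 95% confidence intervals. State that without a comparator the change will not be read as an effect of the programme. If any two-part criterion is kept, say whether one or both parts are required.
2. **Secondary Objectives:** word objective C as describing the change in FTSS during hospitalization.
3. **Discussion, limitations:** add the absence of a control group, naming recovery, hospital-related decline and familiarity with the test as alternative explanations.
4. **Discussion, final paragraph:** call the FTSS change a planning signal instead of an observed beneficial effect. Whether a favourable signal stays as an additional condition for the larger study is the sponsor's choice.

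The cost is wording only. The sponsor gives up a benefit claim on a secondary objective that the design could not support.

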Staying active prevents functional disabilities, particularly in older patients who are hospitalized [11]. These patients quickly lose their ability to perform daily acts by themselves, such as getting up from a low position or walking, causing them to become severely sedentary [6-8,12]. In this context, an intervention can be considered a secondary or tertiary prevention (ie, taking place after confirmation of early-stage risk factors, such as frailty or a history of falls) rather than a primary prevention (ie, before the onset of the disease) [13].

Considering (1) the preventive strategy adopted (ie, the evaluation associated with a mono- or multicomponent intervention), (2) the category of person targeted, and (3) where the intervention takes place (ie, in a home, institution, or hospital), it is important to ensure that the proposed intervention is feasible and usable for the person or the group of people concerned. This is particularly important considering the frailty of older inpatients and the availability of the health care team.

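### The FTSS rule for secondary objective C draws a benefit conclusion from before/after change without a comparator, although the change expected without the programme is unknown

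*Protocol article*

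**What the plan says.** Under Secondary Objectives, objective C is to "examine the effects of this physical activity intervention on the patients’ lower-limb strength". It compares FTSS ability and time at the inclusion assessment with those on the last hospital day, or on day 20 if the patient is still in hospital.

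Secondary Outcome Measures turns this into a verdict: "We will consider the intervention beneficial for patients’ lower-limb strength in two cases". The first is "if the patients can complete the FTSS test more often after the intervention than before"; the second is "if those who complete the FTSS test can do so more quickly after the intervention than before".

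The Design section says: "There is no comparator group (ie, no control group".

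Two sentences under Context describe the expected course of such patients: "Staying active prevents functional disabilities, particularly in older patients who are hospitalized", and "These patients quickly lose their ability to perform daily acts by themselves, such as getting up from a low position or walking".

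The Discussion gives the FTSS result a use. If the usability hypotheses are verified and "if we observe a beneficial effect for the patients, we will plan a larger-scale experiment".

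**The concern.** The rule reads a within-patient change as an effect of the exercises. That is valid only if patients would, on average, have stayed the same without the programme. The article neither states nor supports this, and its Introduction points away from it: rising from a low position, which is close to what FTSS measures, is named as an ability that inpatients quickly lose.

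The conclusion could therefore fail in two directions, which rest on different grounds.

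- **Prevented decline.** If function would otherwise fall, a programme that holds patients at their inclusion level has worked, yet it shows no gain. This follows closely from the article's own premise.
- **Improvement from other causes.** The first test is taken during an acute admission, with reasons that include organ failure and falls, and the second at the end of the stay. Treatment of the admitting illness could improve FTSS. So could familiarity with the test, since daily exercise 3 is nearly the same task. The article does not say that this happens, but a single arm cannot exclude it.

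At stake are the conclusion on objective C and one of the two conditions named for planning a larger study.

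**Working it through.** The article gives no expected change, effect size or power for the FTSS rule, so there is no figure to reproduce. The check has two parts.

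**1. Does anything else in the article supply the missing reference?**

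- *Adjustment.* The Primary Objective Analysis section offers a multivariate analysis to estimate the effect of physical activity, adjusted for age, sex and reason for hospitalization. Every participant is offered the programme, so these covariates cannot show what would have happened without it.
- *Testing.* The General statistics section sets a two-sided 0.05 level. A test against zero change asks whether change occurred, not what caused it.
- *External reference.* None is given.
- *Limitations.* The list in the Discussion does not mention the missing comparator.

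**2. What does the rule respond to?** This illustrates the completion criterion only.

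Inputs from the article: 266 enrolled; fall risk groups of 75, 105 and 85. Assumed, because the article gives no rates: the proportion *a* who cannot do the test before but can after, and the proportion *b* who can before but cannot after. All patients are taken to have both tests.

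Let D = gains − losses. The criterion as written is met when D > 0.

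- Mean of D = n(a − b)
- Variance of D = n[a + b − (a − b)²]
- P(D > 0) ≈ Φ[(mean − 0.5)/SD]

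*Scenario A, no exercise effect, a = 0.15, b = 0.05.* At n = 75: mean 7.5; variance 75 × (0.20 − 0.01) = 14.25; SD 3.77; Φ(7.0/3.77) = Φ(1.85) ≈ 0.97. At n = 266: mean 26.6; SD 7.11; Φ(26.1/7.11) = Φ(3.67) ≈ 0.9999.

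*Scenario B, a 10-point net decline halved to 5 points, a = 0.05, b = 0.10.* At n = 75: mean −3.75; variance 75 × (0.15 − 0.0025) = 11.06; SD 3.33; Φ(−4.25/3.33) = Φ(−1.28) ≈ 0.10. At n = 266: mean −13.3; SD 6.26; Φ(−13.8/6.26) = Φ(−2.20) ≈ 0.014.

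*Scenario C, decline fully prevented, a = b = 0.10.* The mean is 0, so the criterion is met only by chance.

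Exact multinomial results:

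| n | A: D > 0 | A: D > 0 and exact McNemar p < 0.05 | B: D > 0 | C: D > 0 |
|---|---|---|---|---|
| 266 | 99.99% | 95% | 1.3% | 47% |
| 105 | 98.9% | 57% | 7.0% | 46% |
| 85 | 97.8% | 47% | 8.7% | 45% |
| 75 | 97.0% | 41% | 9.8% | 45% |

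Scenario A depends on how much patients improve. With 12.5% gaining and 7.5% losing (net +5 points, again no exercise effect), D > 0 in 96% of trials at n = 266 and in 80% to 85% at n = 75 to 105.

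In scenario C, a fully protective programme gives the same result as an inert programme in patients whose function does not change. The rule follows net change, not the effect of the exercises.

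**The case against.** Several points on the other side are sound.

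- **Improvement is a legitimate target.** The article also speaks of restoring muscle function and describes the exercises as strengthening the lower limbs. A reader might infer from the Introduction that prevention of decline is the only aim and that a rule looking for gain contradicts it. The text does not support that. The problem is the reference level, not that improvement is looked for.
- **Recovery under usual care is not stated.** A reader might infer that the article's premise means natural recovery will be credited to the exercises. It does not: a premise of decline would make an observed gain more persuasive. The recovery argument rests on the acute inclusion test and the missing control, and remains an inference.
- **The rule does not say that an unmet criterion means no benefit.** It says only when benefit will be claimed.
- **The percentages are illustrative.** They rest on assumed rates, complete paired data and one of two criteria. It is unclear whether either criterion suffices or both are needed. If both are, the figures are not the probability of the overall verdict. Requiring a significance test lowers scenario A in the smaller groups to 41% to 47%.
- **The setting is modest.** This is the last secondary objective of an openly uncontrolled usability trial. The Discussion elsewhere speaks of potential benefits, and a positive result leads to further study, not to adoption.

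These points limit the claim and its weight. They do not supply the missing comparison. Both criteria, alone or together, measure change from the same inclusion value, and a significance test does not alter what that change can be attributed to.

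**Conclusion.** The point stands as a fault in the conclusion attached to the data, not in the choice of a single arm for the primary objective. Followed exactly, the rule can produce a causal statement that the design cannot support. It can also fail to register a programme that works by preventing the decline the Introduction describes.

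Under the assumed rates, the completion criterion is met in nearly all trials with no exercise effect when patients improve by a net 10 points, and in at most about one in ten when a 10-point decline is halved. These figures show how the rule behaves; they do not predict this trial's result.

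Severity is moderate. The primary usability outcome and secondary objectives A and B are untouched. The plan to proceed is a statement of intent in the Discussion, not a formal decision rule. The article reports that the results have not yet been analysed, so the wording can still be corrected.

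**What to change.** - **Secondary Objectives and Secondary Outcome Measures.** Replace the language of effects and the benefit verdict with a description of FTSS change during the stay. Give the share of patients who gained, maintained or lost the ability, and the within-patient time change in those completing both tests, with 95% confidence intervals by fall risk group. The article already plans a table of FTSS completion counts by group at the start, on day 6 and at the end, so this extends it.
- **Same sections.** State that, without a comparator, the change cannot be attributed to the intervention.
- **Discussion.** Add the missing comparator to the limitations. In the paragraph on the larger study, treat the FTSS result as supportive description, not as an observed beneficial effect.

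The cost is some rewording and a fuller descriptive table, with no new data. The trial gives up a secondary claim of benefit that its design cannot support.
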